## Abstract

**Background:**

SiFAr-Stress investigates the impact of cycling on stress levels in older adults. Uncertainty due to change to motorized bicycle or fear of falling can be perceived as stressors for cyclists. Stress activates different physiological signal cascades and stimulates the hypothalamic-pituitary-adrenal (HPA) axis, which leads to the release of the stress hormone cortisol and further effects such as the development of low-grade inflammation. Both can—in the long term—be associated with negative health outcomes. The aim of the study SiFAr-Stress is to analyze inflammatory processes as well as the activity of stress systems before and after a cycling intervention for older adults.

**Methods:**

In this study, community-dwelling older adults aged 65 years and older will be randomly assigned to either a cycling or a control intervention in a parallel-group design. Objective HPA axis–related measures (saliva cortisol and hair cortisol) will be assessed before, after, and 6–9 months after the cycling and control intervention (T0, T1, and T2). Furthermore, changes in cortisol reactivity in response to the cycling intervention will be investigated at the second and seventh training lessons. Furthermore, secondary outcomes (fear of falling, perceived stress, salivary alpha amylase, and C-reactive protein) will be assessed at T0, T1, and T2.

**Discussion:**

The study will be the first, in which stress- and health-related bio-physiological outcomes will be assessed in the context of a multicomponent exercise intervention, addressing cycling in older adults. It will enable us to better understand the underlying patho-physiological and psychological mechanisms and will help to improve interventions for this target group.

**Trial registration:**

ClinicalTrials.govNCT04362514. Prospectively registered on 27 April 2020

## Administrative information

Note: the numbers in curly brackets in this protocol refer to SPIRIT checklist item numbers. The order of the items has been modified to group similar items (see http://www.equator-network.org/reporting-guidelines/spirit-2013-statement-defining-standard-protocol-items-for-clinical-trials/).

## Introduction

### Background and rationale {6a}

The demographic change leads to a higher proportion of older persons in the population. Therefore, healthy aging and maintenance of independence are of crucial importance in older adults [1]. Healthy aging is defined as “the process of developing and maintaining functional ability that enables well-being in older age” by the World Health Organization [2]. Positive health and health-related quality of life are highly associated with mobility in older adults [3]. Receiving the ability to live independently and participating in social life requires maintenance of mobility [4–6].

In recent years, cycling as part of daily life mobility has become increasingly popular especially in community-dwelling older adults. Health benefits of cycling [7] as moderate physical activity have been shown in all age groups [8]. Since pedelecs assist cyclists, even more people benefit from this sustainable and environment-friendly locomotion and its positive effect on health and its impact on well-being [7, 8]. In older adults and in middle-aged persons, several studies have shown the beneficial effects of cycling on fitness, cardiovascular health, physical performance, and metabolic processes. Furthermore, cycling in older age can assist in maintaining mobility and, therefore, contribute to living independently and participating in social activities. In contrast, increased bicycle use as well as inappropriate behavior of cyclists and significant traffic growth can result in an increased number of accidents of older adults [1]. Feeling not safe due to road traffic, cycling-related concerns in general, change to motorized bicycle, or lack of practice can be perceived as stressors for cyclists. Until now, no research has been conducted if concerns of cycling can result in chronic stress. Furthermore, the construct of fear of falling (FoF) has been little investigated in the context of cycling-related concerns in older adults so far. Cycling-related concerns address negative outcomes like falls and accidents, and therefore, the construct of FoF (investigated in the context of fall prevention) might be an appropriate way to investigate concerns of cycling.

On the one hand, FoF is associated with several negative outcomes including falls, depression, decreased social contact [9], and reduced quality of life (QoL) [10]. On the other hand, Allali et al. [11] described FoF as a protective mechanism for persons with gait difficulties to avoid activities their motor limitation makes unfeasible. This could mean that cycling concerns result in protective behavior reducing cycling accidents.

Cycling concerns might be associated with chronic stress. Stress arises if individuals are uncertain and lack control about which strategy they should use to cope with the situation [12]. Research on bio-psychological effects of stress found that chronic stress, as well as long-term exposure to anxiety and depressive symptoms, alters the basal activity of the major stress systems [13, 14].

Stress activates different physiological signal cascades, which—in the long term—can be associated with negative health outcomes. Two pathways dominate the acute stress response. The first, which starts immediately after the onset of the stressor, is the activation of the sympathetic nervous system (SNS). This leads to the release of the catecholamines adrenaline and noradrenaline. The second stress response, which peaks with a short delay of a few minutes (about 20 min for socially evaluative stressors) after the onset of the stressor, is the activation of the hypothalamic-pituitary-adrenal (HPA) axis. This leads to the release of glucocorticoids (i.e., cortisol in humans or corticosterone in rodents) from the adrenal cortex. For physical stressors of medium or low intensity (i.e., running, cycling, or strength training) [15–17], only SNS (but not the HPA axis) responses have been reported. However, situations that are associated with anxiety can lead to both, SNS and HPA axis responses. Another physiological stress response that is activated with a delay of a few hours after the onset of acute stressors is the release of pro-inflammatory cytokines (e.g., interleukin-6 (IL-6) and C-reactive protein (CRP)).

Chronic stress alters the basal activity of the major stress systems HPA axis and SNS, which translates to downstream changes in the inflammatory system, ultimately contributing to the development of low-grade inflammation [13]. Therefore, these stress responses are not a health risk factor per se but can lead to negative health outcomes in the long term when people are not able to cope with the stressors. Therefore, chronic stress is associated with an increase in peripheral inflammatory activity [18, 19]. This leads to elevated levels of the stress hormone cortisol and of inflammatory markers such as CRP. Note that for cortisol, very intense and prolonged stress can result in the opposite pattern (i.e., a HPA axis hypo- instead of hyper-activity). However, in the context of daily life stressors, hyper-activity could be expected. Low-grade inflammatory processes might be the link between chronic stress and disease, because stress is associated with low-grade inflammation [13], which is the key factor for morbidity, mortality [20], and predictor for many age-related diseases [21]. In older adults, a state of low-grade inflammation was observed being related with increased plasma levels of pro-inflammatory cytokines such as tumor necrosis factor-α, IL-6, and CRP. These cytokines are associated with an increased risk of muscle strength loss. Physical activity might therefore have a positive effect on muscle loss as well as on chronic stress reduction, which could lead to a reduction of the pro-inflammatory level.

Stress axis activity can be assessed by means of non- or minimally invasive assessment techniques. An established marker for SNS activity is salivary α-amylase (sAA), which can be measured in saliva samples. Salivary α-amylase has been shown to be a well-suited non-invasive marker to investigate SNS reactivity in response to acute stressors. Cortisol levels—as a measure for HPA axis activity—can also be assessed from the saliva. Salivary cortisol has been shown to be associated with plasma cortisol levels and is, therefore, an established marker for HPA axis activity measurements [22, 23]. Collecting bedtime sample on two consecutive days is an accepted and robust way to assess diurnal cortisol output by collecting two saliva samples only. This variable can be used as a marker for general HPA axis activity, which is relatively stable over several days up to a few weeks [14]. A biomarker for systemic long-term stress (up to 3 months, depending on the analysis procedure) is hair cortisol concentration (HCC), which reflects accumulative activity of the HPA axis [24]. Recent or long-term stress is associated with increased hair cortisol levels [25]. Hair is growing constantly about 1 cm per month, which allows HCC to be determined retrospectively over the last months [25].

Inflammatory markers such as CRP levels are usually assessed in blood samples. One minimally invasive procedure is the collection of capillary blood samples by means of dried blood spots (DBS) [26–28]. The DBS method has been shown to be well suited for the assessment of CRP levels [26, 27] and is established in bio-psychological research.

In this study, we investigate the change of inflammatory status as well as stress level in response to cycling as part of physical activity, since in general, physical activity has demonstrated a positive influence on the stress level [29]. The multicomponent exercise program addressing cycling in older community-dwelling persons in the SiFAr study (Siebentritt H, Keppner V, [name], [name], Rappl A, [name], et al. Safer cycling in older age (SiFAr): a protocol of a randomized controlled trial. BMC Geriatr. 2021. submitted) will be used to directly test whether FoF as a surrogate parameter for cycling-related concerns can be related with the stress system activity and with inflammation. We will test whether in the intervention group FoF, psychological symptoms including stress, anxiety, or depressive symptoms can be reduced and whether a reduction of inflammatory response can be reached. Therefore, cycling in older persons will be investigated from a holistic approach in our study. To the best of the authors’ knowledge, no research has been conducted to investigate the abovementioned pathway.

### Objectives {7}

The aim of the study is to investigate the acute and chronic physiological stress-related health benefits of a cycling intervention in older adults. The analysis of the patho-physiological parameters involves two parts: first, the effects of an 8-week cycling exercise training program on general cortisol and CRP levels and, second, the investigation of the acute physiological effects of a cycling training on cortisol and sAA as stress-related health outcomes. We hypothesize that the cycling intervention will have stress-reducing and health benefits in the long term. Furthermore, we hypothesize that the acute cycling training will be a physical stressor, which will be perceived as a stressor associated with anxiety (leading to HPA axis responses) at the beginning of the training. We expect that at the end of the intervention, the training will be a physical stressor only. This reduced acute stress should lead to a general reduction of cortisol levels.

Therefore, as a primary outcome, the following hypotheses will be tested:
Cortisol (measured in the saliva at bedtime and in the hair) will decrease significantly after the intervention in comparison with the control group.

Our secondary hypothesis is that the acute effects of a cycling training on salivary cortisol levels (as a marker for HPA axis activity) will be compared between the beginning and the end of the intervention and will be lower after the seventh than after the second lesson.

Furthermore, we will explore the following parameters to understand better the psychological adaptations to the cycling training: changes in fear of falling and perceived stress before and after the intervention. Moreover, the acute effects of the training on salivary alpha amylase, perceived stress, and anxiety will be investigated.

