### Outcomes {12}

The primary outcome is the change in cortisol and between the beginning of the intervention (T0) and after the intervention (T1). As secondary outcomes, the mean changes in fear of falling (FES-I) and psychological parameters (sAA, CRP, stress (PSS)) over a period of 3 months (after the intervention) and after a follow-up period of 6 to 9 months will be analyzed. Furthermore, the acute effects on cortisol levels during a session at the beginning and at the end of the training intervention (Tr1 and Tr7) will be assessed.

Cycling accidents during the intervention period present a potential risk for the participants and therefore might be a potential harm outcome.

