### Sample size {14}

For statistical analyses of the primary and secondary outcomes, 2-factorial repeated measures ANOVAs are planned (see {20a}). A power analysis for this statistical procedure has been conducted for sample size estimation (GPower 3.1.9.2). Due to the heterogeneity of older persons, the effect size (ES) in this study is estimated to be small to moderate (*f* = .3). With an *α* = .05 and power 1 − *β* = .80, the estimated sample size needed for this effect size is approximately *N* = 111 for a between-group comparison between IG and CG with a 1:1 allocation and three measurement time points. Based on an estimated drop-out rate of 20%, a sample size of *N* = 140 will be adequate for the main objective of this study and should allow for the expected drop-out rate.

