## Statistical methods

### Statistical methods for primary and secondary outcomes {20a}

Data analysis will be performed using descriptive statistical analysis and inferential statistics. The sample data will be presented by frequencies or percentages, means ± standard deviation or median and interquartile range, and graphics. The IBM® SPSS® Statistics for Windows, version 26 software (IBM Corp., Armonk, NY, USA) will be used for all statistical analyses.

For the evaluation of primary outcomes, 3 × 2 analyses of variance for repeated measurements (ANOVA) will be used: For evaluating the long-term changes in CRP and cortisol (hair and saliva), 2-factorial ANOVAs with the factors “time point” (T0, T1, T2) and “group” (IG or CG) will be conducted. For the evaluation of the acute effects of the training intervention, further ANOVAs with the factors “time point” (before, after, and 20 min after the training) and “training number” (second or seventh training) will be calculated. For the evaluation of further secondary outcomes, comparable analyses will be conducted.

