## Discussion

### Potential risks and limitations

Due to the COVID-19 pandemic, the intended number of participants might not be reached. To meet this challenge, we established a hygiene concept, which allows performing the assessments. Cycling lessons will take place outside allowing almost contactless saliva sampling for acute phase measurements. SiFAr will have to recruit almost double of participants in the same time, which allows to meet the number of 140 for SiFAr-Stress according to a participation rate of the last year.

The number of hair specimen might be insufficient to reach statistically valid analysis, because short hairstyle, thinning hair, or be bald prevail among community-dwelling older adults. In this case, hair specimen sampling is impossible and only CRP and salivary cortisol will be evaluated for these participants.

Many factors are known to potentially influence saliva cortisol measurement, like tooth brushing, eating, drinking caffeinated drinks, and ordinary physical activity. We therefore ask participants to avoid eating, drinking (except water), smoking, chewing gum, and brushing teeth for at least 1 h before saliva sampling, but they might not always adhere to this request.

For biological samples, informed consent will be obtained individually for saliva, hair, or capillary blood samples or all of these together. Participants will not be excluded from the substudy, if not all three samples can be obtained. Information on medication is collected of all participants, and all participants with glucocorticoid medication will be excluded from the cortisol analysis. Oral intake of glucocorticoids influences the cortisol measurement. To limit this potential risk factor, information on medication is collected from all participants, and all participants with glucocorticoid medication will be excluded from the cortisol analysis. Cortisol levels over 100 nmol/l will be excluded as outliers, which indicates an oral intake of glucocorticoids. These saliva specimens will be exclusively analyzed for alpha amylase.

Intake of medication containing beta-blockers influences the alpha amylase measurement and will be excluded for the alpha amylase analysis and exclusively used for cortisol measurement. If hair specimen sampling is impossible, only CRP and salivary cortisol will be evaluated for these participants.

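### The primary outcome is defined three ways, and no rule says whether salivary cortisol, hair cortisol or both must fall, while the sample size allows for one test at .05

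*Protocol article*

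**What the plan says.** Four sections of the protocol article bear on the primary outcome.

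- **Objectives {7}** names two specimens in one primary hypothesis: "Cortisol (measured in the saliva at bedtime and in the hair) will decrease significantly after the intervention in comparison with the control group".
- **Outcomes {12}** names no specimen, and the sentence appears to have lost a word: "The primary outcome is the change in cortisol and between the beginning of the intervention (T0) and after the intervention (T1". It places CRP among the secondary outcomes, under "psychological parameters (sAA, CRP, stress (PSS".
- **Statistical methods {20a}** opens with "For the evaluation of primary outcomes, 3 × 2 analyses of variance for repeated measurements (ANOVA) will be used" and continues "For evaluating the long-term changes in CRP and cortisol (hair and saliva), 2-factorial ANOVAs". CRP therefore stands beside the two cortisol markers straight after the primary lead-in.
- **Sample size {14}** gives alpha .05 and power .80 once, for f = .3: "A power analysis for this statistical procedure has been conducted for sample size estimation (GPower 3.1.9.2". The result is 111, raised to 140 for 20% drop-out. Alpha is neither divided nor ordered.

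On hair, Potential risks and limitations warns: "The number of hair specimen might be insufficient to reach statistically valid analysis". The fallback given there is for the individual participant: where hair cannot be taken, only CRP and salivary cortisol are evaluated. It does not say what then becomes of the primary hypothesis. The consent provisions {26b} also let participants decline a specimen type.

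**The concern.** A reader cannot tell from the protocol what result would count as success. Suppose salivary cortisol falls relative to control and hair cortisol does not. The Objectives wording can be read as a failure, because both were named, or as a success on one of two primary markers. The Outcomes wording settles neither.

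Such a split is plausible on the protocol's own account. The background describes bedtime saliva as stable over days to a few weeks, and hair as accumulated activity over up to three months. The two markers need not move together.

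If either marker suffices, the chance of a false positive primary claim exceeds .05. If both are required, the trial lacks its stated power. If the rule is chosen once results are known, the primary claim loses its confirmatory standing.

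**Working it through.** **Inputs from the protocol article:** f = .3, alpha = .05, power = .80, three time points, 111 evaluable, 20% drop-out, 140 recruited (Sample size {14}); two cortisol markers (Objectives {7}).

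**Assumptions, because the documents give no figure:** the correlation between the two test statistics (0 to .8) and the share of participants with usable hair (50% to 90%).

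**1. The plan's own figure.** With noncentrality f² × N = .09 × 111 = 9.99, 2 numerator and 108 denominator degrees of freedom, and one test at .05, power is .803. At N = 110 it is just under .80, so 111 reproduces. Drop-out: 111 / .80 = 138.75, so 139, consistent with 140.

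This variant uses no repeated-measures correlation and does not match the between-group comparison that the section describes. It is used below only because it returns 111. In this variant, 111 is the size for a single test at the full .05.

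**2. Either marker suffices, each tested at .05.** If independent, the family-wise error is 1 − .95² = .0975. For correlated two-sided normal tests it is 1 − P(|Z1| < 1.96 and |Z2| < 1.96).

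**3. Both markers required, each with 80% power.** If independent, joint power is .80² = .64. With correlation it is the bivariate normal probability that both tests reject.

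| Correlation | Family-wise error (either) | Joint power (both) |
|---|---|---|
| 0 | .0975 | .640 |
| .3 | .095 | .666 |
| .5 | .091 | .687 |
| .8 | .078 | .729 |

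Under full dependence the error returns to .05 and joint power to .80.

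**4. Cost of keeping both markers primary, in the variant that reproduces 111.**

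- Either, with Holm: the first step is at .05 / 2 = .025. Power per marker at that step falls from .803 to .714 at N = 111. Restoring 80% at .025 takes 132 evaluable, and 132 / .80 = 165 recruited.
- Both at .05: joint power at N = 111 is .8035² = .646 if independent. For 80% joint power, 142 evaluable are needed, and 142 / .80 = 177.5, so 178 recruited.

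**5. Hair loss, same variant, alpha .05.** If hair is usable in the stated share of the 111:

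| Share with hair | N | Power for hair |
|---|---|---|
| 90% | 100 | .76 |
| 80% | 89 | .70 |
| 70% | 78 | .64 |
| 60% | 67 | .57 |
| 50% | 56 | .48 |

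These shares only illustrate the sensitivity; they are not forecasts.

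**The case against.** The strongest reply is that this is a condensed article and its analysis plan is not shown. How alpha is allocated is commonly left to that plan, so its absence here is no fault. That stands. It does not cover the choice of primary variable, for which the article has its own section, and which three sections state in three ways.

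The second reply is that the Objectives sentence joins saliva and hair with the word and, so that both must fall. On that reading the type I error is controlled. This also stands: inflation arises only under the either reading, which no section states. But the both reading is not stated as a rule, and it carries the power loss shown above.

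Several stronger readings are tempting and are not supported:

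- **Each marker is to be tested at .05.** The article never says so. It is inferred from one undivided alpha for a procedure applied to each outcome.
- **CRP is a third primary outcome.** The abstract and Outcomes {12} call it secondary. The paragraph in {20a} also holds the acute training analyses, which Objectives {7} calls secondary, so its lead-in is loose. CRP is inconsistently classified, and a three-test error rate should not be charged to the primary claim.
- **Group main effects add further chances of success.** The hypothesis concerns a decrease relative to control, which a main effect averaged over time does not test. Nothing says that such an effect would count.
- **The trial expects to lose hair.** The text says only that numbers might be insufficient.
- **The hair sample at T1 is invalid because it spans the early lessons.** A randomised comparison of accumulated exposure is legitimate, and no figure shows that the early weeks would dominate. The differing time windows show only that the markers may disagree.

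**Conclusion.** The point holds as an unresolved definition of the primary outcome. The sections disagree on which variables are primary, no success rule is given for the two cortisol markers, and the sample size allows for one test at .05. If either marker suffices, the family-wise error is about 9.1% to 9.75%. If both are required, alpha is kept and joint power is about 64% to 69%. Both ranges assume correlations from .5 down to 0, and both narrow towards the stated .05 and .80 only as the tests approach full dependence. The joint-power range takes the stated 80% per marker at face value and does not allow for missing hair, which would lower it further. The status of CRP is a wording conflict between {12} and {20a}, to be corrected with the rest.

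**What to change.** Before any group-level results are seen, name one primary outcome for the change from T0 to T1, in the same words in Objectives {7}, Outcomes {12} and Statistical methods {20a}. Bedtime salivary cortisol is the natural choice, because the protocol itself doubts the hair numbers. Make hair cortisol the first secondary outcome. Move CRP out of the primary wording in {20a} so that it agrees with {12}. The cost is a documented change of wording and the loss of primary status for hair; 111 and 140 are unchanged.

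If both cortisol markers are to stay primary, state the rule and its price:

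- **Either marker suffices:** use Holm and restate power per marker, about .71 at the .025 first step with 111 evaluable. This is not a small loss. Keeping 80% at that step would take about 132 evaluable and 165 recruited.
- **Both markers required:** make no alpha adjustment, but restate joint power as about 64% to 69% under the assumed correlations, less any hair loss. Keeping 80% would take about 142 evaluable and 178 recruited if the tests are independent.

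The restated sizes use the variant that reproduces 111 and should be recalculated if the sample-size method itself is revised.
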